### Analysis methods

#### RCT

Data from the RCT will be analysed once data collection is complete. Descriptive summary statistics of baseline characteristics and process variables (e.g. number of education sessions available, back end data for the Toolkit and MyDesmond websites, usual care delivery, etc.) will be produced, using mean (standard deviation) for normally-distributed variables, median (interquartile range) for non-normally distributed variables, and count (percentage) for categorical variables.

The primary analysis will compare HbA1c between the control and intervention states using a mixed model that allows for repeated longitudinal outcomes and practice-level clustering, and is adjusted for season to deal with expected seasonal variation in HbA1c. The primary analysis will be based on the intention-to-treat (ITT) population, i.e. all eligible patients will be included. Missing outcome data will need to be imputed for the ITT analyses. This will be done using an appropriate multiple imputation method; it is anticipated that predictive mean matching will be used to impute continuous outcomes as this is able to handle non-linearity and non-normality, and logistic regression will be used for binary outcomes. Predictive variables are likely to include practice level demographics, e.g. sex, ethnic group, or baseline HbA1c. Sensitivity analyses will repeat the primary analyses using complete cases and per protocol populations.

As secondary analyses, the ITT model from the primary analysis will be fitted for the following subgroups of interest: (1) including only patients who attended education; (2) excluding patients with HbA1c < 6.5% at baseline; (3) by baseline education attendance status; (4) by patient ethnicity and age to examine the effectiveness of the Embedding Package in groups in which there is low SSME uptake; (5) by type/format of programme offered/attended.

Secondary patient-level and practice-level outcomes will be compared in a similar manner to the primary analyses, except that practice-level outcomes will not be adjusted for cluster and the psychosocial outcomes will not account for repeated measures as they will only be measured once.

Summaries of self-reported referral and attendance will be produced using appropriate descriptive statistics for the whole dataset and by pertinent subgroups, such as sex and age. Data on SSME referrals and attendance will also be compared between data sources (i.e. self-report, practice, and provider).

A full statistical analysis plan will be written and agreed by all investigators and the trial steering committee before the data are released for analysis. Statistical significance will be defined as *p*-values less than 0.05.

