#### RCT design (months 0–18)

Baseline data have been collected at month 0. Practices will be randomised 1:1 to 1) the immediate group who receive the Embedding Package from months 0 to 18, or 2) the wait-list group who provide usual care for months 0–9 and receive the Embedding Package for months 9 to 18 (Fig. 1). Since data are collected from each step, each practice acts as its own control (immediate group uses the baseline data as its control, the wait-list group uses data collected between 0 and 9 months). To limit potential contamination, for the aspects of the intervention that are targeted at CCG/locality/provider level (e.g. social marketing initiatives), we will request that as far as possible, these are first targeted at practices participating in the Embedding Package, and only aimed at wait-list practices when these have crossed over to receive the intervention.

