#### Primary outcome

The primary outcome is patient-level HbA1c compared between the control and intervention conditions in the RCT i.e. the baseline measure in the immediate group, and baseline and first step in wait-list group compared with first and second steps in immediate group and second step in wait-list group.

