### Control

Usual care will be practice-dependent; therefore, each practice will continue to provide their usual activities related to SSME whilst in the control period. These activities vary greatly between CCGs and their associated practices, and due to the ever-changing landscape of the NHS, usual care may evolve over time. However, usual care will be monitored and recorded within all practices.

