### Randomisation

This is an open-label trial as it will not be possible to blind practices to their treatment arm. Practices will be randomised prior to baseline (month 0) in a 1:1 fashion to either: Immediate group (receive the Embedding Package for months 0–18), or wait-list group (provide usual care for months 0–9 then receive the Embedding Package for months 9–18). Randomisation will be stratified by CCG, and generated and implemented by a statistician. The statistician will provide the study team with the randomisation outcome so that they can inform practices of their allocation.

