### Sample size

In the feasibility study an average cluster size of 460 was found across the six practices included (range 118–824) (Davies et al. Increasing uptake of self-management education programmes for type 2 diabetes in a multi-ethnic primary care setting: A feasibility study. 2019. In preparation). Recruiting 58 practices (29 to each randomisation point) will give over 90% power to detect a difference in HbA1c of 0.1% assuming an SD of 1.5%, based on United Kingdom Prospective Diabetes Study (UKPDS) [35]. There will be 80% power to detect a difference as small as 0.062%. This assumes an intra-cluster correlation coefficient (ICC) of 0.05, one baseline HbA1c measurement with one more HbA1c measurement at each randomisation point. This calculation does not take account of potential variation in cluster size, as methodological work has shown that the power of studies of a stepped wedge type design is robust to variation in cluster size [36]. The sensitivity of this calculation to changes in the average cluster size was assessed. As long as the average cluster size remains larger than 174 there will be 80% power to detect a 0.1% difference. To allow for potential cluster drop out of 10% the target will be to recruit 66 practices in total.

Return of a completed questionnaire booklet (self-report questionnaire and/or consent to link data form) will be recorded as consent to participate in the study. Additionally stakeholders and patients consenting to ethnographic interviews and observations will be recorded as participants. It is anticipated a minimum of 2050 participants will be recruited (2000 via questionnaire and 50 via interview/observation).

The integrated ethnographic study will be conducted within a sub-sample of approximately 12 of the practices and related contexts (e.g. CCGs and providers). Purposive sampling of practices will take place in the first and second steps of the RCT to ensure a representative sample [22]. A subset of 12 practices will provide data for the cost-effectiveness analysis.

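### The primary model names season but no step effect, although all baseline values are control and all second-step values are intervention

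*Protocol article*

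**What the plan says.** Under Analysis methods, RCT, the primary analysis compares HbA1c between control and intervention states in a mixed model with repeated outcomes, "practice-level clustering, and is adjusted for season to deal with expected seasonal variation in HbA1c". No step, period or calendar-time term is named for it anywhere in the article. The same section says that a full statistical analysis plan will be agreed before data release.

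Primary outcome sets the contrast: "the baseline measure in the immediate group, and baseline and first step in wait-list group compared with first and second steps in immediate group", with the wait-list group's second step also on the intervention side. RCT design (months 0–18) explains where each group's control data come from: "immediate group uses the baseline data as its control, the wait-list group uses data collected between 0 and 9 months".

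The Control section accepts that "usual care may evolve over time". Background calls type 2 diabetes progressive and reports that offers of education to newly diagnosed patients rose from 47.4% in 2013 to 74.5% in 2016.

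Sample size assumes 58 practices, SD 1.5%, ICC 0.05 and one measurement at baseline and at each of the two steps. It claims over 90% power for a 0.1% difference. It adds: "There will be 80% power to detect a difference as small as 0.062"%. It also gives 174 as the average cluster size above which there is 80% power for 0.1%. It does not name the model behind these figures.

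**The concern.** Coding control as 0 and intervention as 1, the immediate group runs 0-1-1 and the wait-list group 0-0-1 over baseline, step 1 and step 2. Intervention values are therefore later, on average, than control values. If the model has no term for step, anything that moves HbA1c in all practices over 18 months is attributed to the intervention. Season does not help: it is cyclic, and the issue is a trend.

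The article itself makes a trend plausible through progressive disease, evolving usual care, and an open cohort whose eligibility is re-assessed at each step. At stake is whether the primary estimate rests on the randomised comparison or mainly on before-and-after change within practices.

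**Working it through.** **Inputs.** From Sample size: 29 practices per group, 460 patients per practice (taken as the number per period), SD 1.5, ICC 0.05, three periods. From Analysis methods: significance level 0.05, taken as two-sided. Assumed: a practice effect that is constant over time, and patients treated as a fresh sample in each period. The drift d per 9-month step is not in the article and is varied below.

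Practice variance τ² = 0.05 × 2.25 = 0.1125. Residual variance of a practice-period mean s² = 0.95 × 2.25 / 460 = 0.004647. Let k = τ² / (s² + 3τ²) = 0.1125 / 0.34215 = 0.3288.

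**1. The plan's own figures, with step effects.** Only the between-group differences at each step are informative, and the groups differ in state only at step 1. Generalised least squares gives

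Var = (2/29) × s² / (1 − k) = 0.06897 × 0.004647 / 0.6712 = 0.000477, so SE = 0.0219.

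- Difference detectable at 80% power: 2.802 × 0.02185 = 0.061 (stated 0.062).
- Power at 0.1: 0.1 / 0.02185 = 4.58, which gives 99.6% (stated over 90%).
- Smallest cluster size for 0.1 at 80%: with 171 patients, s² = 0.0125, k = 0.3214, SE = 0.0356 and 2.802 × 0.0356 = 0.100. So 171 (stated 174). A t reference on about 113 degrees of freedom gives 0.0617 and 174.

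**2. The same inputs without step effects.** There are 29 × 2 + 29 × 1 = 87 practice-periods in the intervention state out of 174. The variance becomes

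Var = s² / (43.5 − 14.5k) = 0.004647 / 38.73 = 0.000120, so SE = 0.0110.

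The detectable difference is 2.802 × 0.01095 = 0.031, and the smallest cluster size is 43. Neither is close to the stated figures.

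**3. Bias when step is left out.** Let HbA1c shift by 0, d and 2d at baseline, step 1 and step 2 in every practice, with no intervention effect.

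- Immediate group, intervention minus control: (d + 2d)/2 − 0 = 1.5d.
- Wait-list group: 2d − (0 + d)/2 = 1.5d.

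The full least-squares result is 58d / (43.5 − 14.5k) = 58d / 38.73 = 1.497d. With SE 0.01095:

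| Assumed d (% HbA1c per step) | Bias | Bias / SE | Rejection under no effect |
|---|---|---|---|
| 0.01 | 0.0150 | 1.37 | 28% |
| 0.02 | 0.0299 | 2.73 | 78% |
| 0.03 | 0.0449 | 4.10 | 98% |

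A drift of 0.1 / 1.497 = 0.067 per step would equal the whole target difference in size.

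**4. Does season rescue it?** Season was entered as four quarters, with practice starts spread from August to February as the Recruitment section's dates imply. At d = 0.02 the bias is still 0.030, the SE 0.0111 and the rejection rate 76–77%. With step effects added and season kept, the bias is 0, the rejection rate 5% and the SE 0.0219.

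**5. Does the constant practice effect matter?** With a cluster autocorrelation of 0.8 to 1.0, the bias multiplier stays at 1.48–1.50. At 0.8 and d = 0.02 the rejection rate is lower but still 20% or more.

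**6. What the step-adjusted estimate uses.** The weights on the between-group differences at baseline, step 1 and step 2 are −k/(1 − k), 1 and −k/(1 − k), that is −0.49, 1 and −0.49.

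**The case against.** The strongest reply is that this is a condensed article. It does not exclude a time term or call its covariate list complete, and it defers to a statistical analysis plan. The design is described as similar to a stepped wedge, and the power figures fit a period-adjusted model, so the authors may have planned step effects and shortened the text. Listing which cells are control and which intervention is also compatible with a step-adjusted model.

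Much of this stands. A reader might infer that the plan has rejected a step effect; the documents show only that none is named. Nor do the power figures prove which model was used: the match is close, only a few models were tried, and the article names none. But the article is not silent on time. It chooses an adjustment, gives the reason for it and names season alone, while the design section presents baseline as the immediate group's control. Someone following that text would fit a model open to trend.

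A reader might also infer that the trial is heading for a false claim of benefit. The documents give neither the size nor the direction of any drift. Progressive disease and an ageing cohort would tend to raise HbA1c, which would hide benefit or suggest harm.

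The objection to the remedy also has force. With step effects, step 2 is subtracted as heavily as baseline, so the estimate does not rest on step 1 against baseline alone. It assumes the same effect after 9 and 18 months of exposure, although the Intervention section allows the package to change at month 9. As an illustration with assumed effects of 0.05 in the first 9 months of exposure and 0.10 in the second, the step-2 difference is 0.10 − 0.05 = 0.05 and the model estimates 0.05 − 0.49 × 0.05, about 0.026.

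**Conclusion.** The concern holds in this form: the stated primary model names season as its only time adjustment and no step effect, in a design where state and time are strongly confounded. Fitted as written, it passes about 1.5 times any common drift per 9-month step into the treatment estimate, in the direction of the drift. The multiplier follows from the design and barely depends on the correlation assumptions. The rejection rates of 28%, 78% and 98% rest on assumed drifts and on a constant practice effect. The analysis and sample-size sections also disagree: the stated power fits a step-adjusted SE of 0.022, while the model as described has an SE of 0.011.

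A reader might infer that adding step effects costs no power whatever the correlation structure. The stated power holds only under the constant practice effect that the sample-size figures appear to use. At an assumed cluster autocorrelation of 0.9, power for 0.1% is about 70%.

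**What to change.** State the primary model as HbA1c on intervention state, with fixed effects for step (baseline, step 1, step 2), season kept as a further covariate, and random effects for practice and patient. In RCT design, clarify that baseline data alone are not the immediate group's control and that the comparison is adjusted for step. Add a sensitivity analysis restricted to baseline and step 1, or one that lets the effect differ by exposure time.

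The cost in text is a few sentences before data release. The SE roughly doubles against the model as written (0.011 to 0.022), but the stated power already fits the larger value, so no more practices are needed under the constant practice effect. On the same assumptions, the analysis restricted to baseline and step 1 would have a detectable difference of 0.070% and about 98% power for 0.1%.

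### For the baseline-defined subgroups (baseline education attendance, ethnicity, age) the protocol names only subgroup-specific fits of the primary model and no intervention-by-subgroup interaction, so the named analysis cannot show whether effects differ between groups

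*Protocol article*

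**What the plan says.** The protocol describes the primary analysis of HbA1c (Analysis methods, RCT) as "using a mixed model that allows for repeated longitudinal outcomes and practice-level clustering, and is adjusted for season". No subgroup term is mentioned. For the secondary analyses it then states that "the ITT model from the primary analysis will be fitted for the following subgroups of interest", followed by five items:

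1. a restricted set, "including only patients who attended education";
2. a restricted set leaving out patients with baseline HbA1c below 6.5%;
3. by baseline education attendance;
4. "by patient ethnicity and age to examine the effectiveness of the Embedding Package in groups in which there is low SSME uptake";
5. by type or format of the programme offered or attended.

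The same section gives a general threshold: "Statistical significance will be defined as *p*-values less than 0.05". It also says that "A full statistical analysis plan will be written and agreed by all investigators and the trial steering committee before the data are released for analysis". That plan is not at hand. No interaction or heterogeneity test is named anywhere in the article, and none is excluded.

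The article gives no subgroup sizes. The Sample size section gives the design inputs used below.

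**The concern.** Items 3 and 4 divide the trial population by characteristics fixed before the intervention. A reader will naturally set the resulting estimates side by side. The Background invites this, since it cites a meta-analysis in which the benefit of structured education was greater in people under 65 and in non-white participants.

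Subgroup-specific fits do not answer that comparative question. A smaller group has a larger standard error, so it can miss p < 0.05 with exactly the same true effect as a larger group that reaches it. The estimates are not biased by subgroup size. What size changes is their precision, and with it the pattern of significant and non-significant results. At stake is what the trial will be taken to say about minority ethnic groups, age groups and people with or without earlier education.

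**Working it through.** **Inputs (Protocol article, Sample size).** 58 practices, 29 per sequence; average cluster size 460; SD 1.5%; ICC 0.05; one baseline measurement and one at each of two steps, so three periods. The protocol states that this "will give over 90% power to detect a difference in HbA1c of 0.1% assuming an SD of 1.5"%, and "There will be 80% power to detect a difference as small as 0.062"%. It also states 80% power for 0.1% as long as the average cluster size exceeds 174. I take alpha as two-sided 0.05; the protocol does not give the sidedness.

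**Step 1: reproduce the protocol's figures.** Sequences are 0-1-1 (immediate) and 0-0-1 (wait-list), with the Hussey-Hughes variance for a cross-sectional stepped-wedge model with period effects:

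Var = I·s²(s² + T·t²) / [(I·U − W)s² + (U² + I·T·U − T·W − I·V)t²]

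- s² = 1.5² × 0.95 / 460 = 0.004647; t² = 0.05 × 1.5² = 0.1125; I = 58; T = 3
- U = 29 × 3 = 87; W = 0² + 29² + 58² = 4205; V = 29 × 2² + 29 × 1² = 145
- I·U − W = 841; U² + I·T·U − T·W − I·V = 1682
- Var = 58 × 0.004647 × 0.34215 / (841 × 0.004647 + 1682 × 0.1125) = 0.000477, so SE = 0.02185

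Power = Φ(difference/SE − 1.96). At 0.1% this is 99.6%; at 0.062% it is 81.0%; at cluster size 174 (SE 0.0353) and 0.1% it is 80.8%. All three agree with the protocol, so this model fits its power statement. The same calculation without period effects gives SE 0.01095 and a difference detectable with 80% power of 0.031%, half the stated 0.062%.

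**Step 2: split each practice into two subgroups with the same true effect.** Cluster size becomes 460 × share in the same formula. With powers P1 and P2, and the two fits treated as independent, the chance that exactly one is significant is P1(1 − P2) + P2(1 − P1). For the 50:50 split at 0.1%: SE 0.0308 in each half, power 90.1% each, and 2 × 0.901 × 0.099 = 17.9%.

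| Split (assumed) | Power at 0.1%, larger / smaller | Exactly one significant, 0.1% | Exactly one significant, 0.062% | Same without period effects, 0.1% | Same without period effects, 0.062% |
|---|---|---|---|---|---|
| 50:50 | 90% / 90% | 18% | 50% | 0% | 4% |
| 70:30 | 97% / 71% | 30% | 55% | 0.1% | 13% |
| 80:20 | 98% / 55% | 46% | 61% | 2% | 28% |
| 90:10 | 99% / 32% | 68% | 69% | 17% | 56% |

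An 85:15 split gives 56% at 0.1% with period effects. The last two columns matter because the analysis text names season, not period, as the time adjustment.

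**Step 3: power of an interaction test.** With period effects, the SE of the between-group difference is √(SE1² + SE2²): 0.0436 (50:50), 0.0474 (70:30), 0.0541 (80:20) and 0.0712 (90:10). Power for a true between-group difference of 0.1% is then 63%, 56%, 46% and 29%. At the two-sided 5% level, such a test declares a difference in 5% of trials when none exists.

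**The case against.** The strongest objection is that the gap is one of silence. The article does not exclude an interaction term, its use of 'by' for items 3 and 4 does not settle how the model is parameterised, and a full analysis plan is promised before data release. This stands in part: it is right to say that no interaction is named, not that none will be fitted. But the article does more than list subgroups. It states a method, the primary model fitted for subgroups, and that method alone cannot support a comparison between them.

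Second, the stated aim of item 4 is effectiveness within low-uptake groups, which a subgroup estimate with its interval addresses. This also stands. A reader might infer that the trial will declare the package effective in one group and not in another by comparing p-values. The documents do not say so: the 0.05 threshold is a general definition, and no rule for comparing subgroups is given. The percentages above therefore describe how often the significance pattern could mislead, not an error rate of a stated decision rule. They are not like for like with the 5% of an interaction test.

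Third, the size of the problem depends on assumed splits, on the true effect and on period adjustment. That is correct, and is why the range is shown. The calculation also treats the two fits as independent; positive correlation between them would lower the discordance.

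Fourth, an interaction test has modest power. True, but that is a reason to label the results exploratory and to report the interval, not to leave the interaction out.

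**Conclusion.** The point holds for baseline education attendance, ethnicity and age. The only method named for them gives within-group effects and does not show whether effects differ. With period effects and a common true effect of 0.1%, two subgroups disagree on significance in about 18% to 68% of trials for splits from 50:50 to 90:10; at 0.062% the range is 50% to 69%. Without period effects the ranges are about 0% to 17% and 4% to 56%. All of this rests on assumed splits, independent fits and two-sided testing.

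Two stronger readings are not supported. A reader might infer that separate fits make the subgroup estimates themselves artefacts of size; they do not, because size affects precision only. A reader might also extend the point to all five items. In the attenders-only analysis, and for programme attended in item 5, patients are selected on something the intervention can change. That selection is the main problem there, and an interaction does not cure it. The exclusion of baseline HbA1c below 6.5% is a restriction with no comparison group.

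The primary analysis is not affected. The change is worth making because it bears on conclusions about the groups that the protocol singles out.

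**What to change.** In the statistical analysis plan, before data release, and for baseline education attendance, ethnicity and age only:

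- fit one model to the full ITT population, being the primary model plus the subgroup factor and its interaction with intervention;
- report the interaction estimate with its confidence interval and p-value;
- present within-subgroup effects from that same model, as description;
- state that any claim of differing effects rests on the interaction alone;
- label these analyses exploratory, citing the limited interaction power.

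This fix should not be carried over to the attenders-only, HbA1c-restricted or programme-attended analyses. The cost is analysis wording only: no new data and no change to the design or sample size.

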## Methods/design

### Objectives

The primary objective of this ambitious mixed methods study is to assess whether the Embedding Package, by increasing uptake and attendance at structured education, reduces HbA1c in people with T2DM compared with usual care. This objective will be addressed through a wait-list cluster RCT.

The secondary objectives are to:
assess whether the Embedding Package increases referral to and uptake of structured education, as well as improving biomedical and psychosocial outcomes;assess sustainability of the Embedding Package using an observational follow-up period;contextualise the process of implementation, sustainability of the change and the ‘fit’ of the Embedding Package within routine practice;assess cost-effectiveness of the Embedding Package.

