#### Secondary outcomes

The secondary biomedical measures to be extracted from primary care at the patient level are: Body Mass Index (BMI); weight; total, Low-Density Lipoprotein (LDL) and High-Density Lipoprotein (HDL) cholesterol; systolic and diastolic blood pressure; glucose, blood pressure and lipid lowering medications; smoking status; hospital admissions; cardiovascular risk score.

Process outcomes will reflect how the intervention is implemented and aid understanding of effectiveness. They will be measured at the patient, practice, or provider level as appropriate, and will include the following: whether or not the patient was referred to and attended SSME (main secondary outcome); type of SSME; percentage of eligible individuals referred to education; percentage of eligible individuals who attended education; percentage of eligible individuals who declined education; number, timing and venue of available education sessions; number of trained educators.

Secondary psychosocial and process outcomes will also be self-reported by a subset of patients at a single time-point during the first step so that psychosocial outcomes can be compared between those in the intervention and control arms (it is estimated around 2000 questionnaires will be returned). This data will be collected by questionnaire; all participants will be sent a short questionnaire they can further opt to complete an additional questionnaire. The self-reported outcomes from the short questionnaire are: whether or not the patient was referred to and attended SSME; and where the patient has previously received diabetes information from. Those completing the additional questionnaire will provide data on patient activation measure; well-being (W-BQ12); Problem Areas in Diabetes (PAID) score.

Additionally, back end website data on the extent of user engagement (e.g. length of time for which individual pages were viewed and the number of occasions etc.) with specific tools in the online toolkit will be collected.

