The trial not only assesses the effectiveness of the intervention but also includes an observational follow up phase. During this time no active trial input will happen, and the follow-up phase will therefore capture whether the Embedding Package can change culture and practice leading to longer term improvements. The trial is also pragmatic; all people with T2DM will be included irrespective of whether they are referred to or attend education during the study period. Therefore a small change in HbA1c is expected. In a study conducted at the patient level, a minimum difference of 0.3% in Hba1c may be clinically meaningful and lead to change in practice. Here the study is powered to detect a difference of at least 0.1%. This reflects the practice-level design of the study. Planned secondary analyses will try to elicit the effectiveness of the intervention in those referred to education during the course of the study. The study uses a wait-list design, similar to a stepped wedge design but with a single step during the study. The design is efficient as each practice acts as its own control and therefore produces a significant reduction in the sample size required compared to a standard cluster randomised trial. Given components of the intervention are delivered at the level of the CCG/providers, strategies to limit contamination of control state practices will be put in place during the first step.

If the Embedding Package is found to be both effective and cost-effective, a ‘toolkit’ to enable widespread implementation will be developed and rolled-out.

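### Secondary analysis (1), and the 'attended' half of (5), select patients on attendance that can follow randomisation, so they are not randomised comparisons and cannot show the effect in attenders

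*Protocol article*

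**What the plan says.** In the protocol article, Analysis methods (RCT), the primary analysis uses the "intention-to-treat (ITT) population, i.e. all eligible patients will be included". For the secondary analyses, "the ITT model from the primary analysis will be fitted for the following subgroups of interest", and five entries follow. The first is "1) including only patients who attended education" and the fifth is "5) by type/format of programme offered/attended". The third, "3) by baseline education attendance status", is a separate entry, so the first is not the baseline-attendance subgroup.

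Attendance has two further roles in the article:
- Under Objectives, the question is whether the package, "by increasing uptake and attendance at structured education, reduces HbA1c in people with T2DM compared with usual care".
- Under Secondary outcomes, the process measures begin with "whether or not the patient was referred to and attended SSME (main secondary outcome").

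The Discussion gives the secondary analyses a purpose: "Planned secondary analyses will try to elicit the effectiveness of the intervention in those referred to education during the course of the study".

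No time limit is put on 'attended' in the first entry. Table 3 takes the last recorded attendance code with its date. It does not limit this to the measurement period, as it does for HbA1c. Data collection says that months 9 and 18 are extracted together.

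**The concern.** A subgroup contrast keeps the protection of randomisation only if allocation cannot influence membership. Membership by attendance fails that test, because the package exists to change who attends. Control-state attenders came under usual care. Intervention-state attenders also include people whom the package drew in. The two sets may differ in motivation, disease duration and HbA1c for reasons unrelated to any benefit.

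The article expects a small overall change because it includes everyone with type 2 diabetes. If that is what is found, a reader will look to the attender result for the effect in those who took part. As planned, that result could show nothing when education works, or a benefit that is only selection and time.

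**Working it through.** **1. The two possible meanings of item (1)**
- *Attendance counted per step.* Control-state and intervention-state patients in the model have both attended. The education effect is on both sides and largely cancels. It does not cancel entirely, because the last HbA1c in a step may precede attendance. What remains is the difference in who attended.
- *Attendance counted at any time.* Records from before attendance enter, mostly in the control state, and records from after it mostly in the intervention state. This is largely a before-after comparison in self-selected patients. The only time-related adjustment that the article names is season.

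**2. The plan's own precision, reproduced**

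Inputs from Sample size: 58 practices (29 per arm), 460 patients per practice, SD 1.5, ICC 0.05, and one baseline plus two later measurements. A two-sided 5% level is assumed. The model is the standard stepped-wedge mixed model with fixed period effects and sequences 0-1-1 and 0-0-1:

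Var = Iσ²(σ² + Tτ²) / [(IU − W)σ² + (U² + ITU − TW − IV)τ²]

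- I = 58, T = 3, U = 29×2 + 29×1 = 87, W = 29² + 58² = 4205, V = 29×4 + 29×1 = 145
- τ² = 0.05 × 2.25 = 0.1125; σ² = 0.95 × 2.25/460 = 0.004647
- IU − W = 841; U² + ITU − TW − IV = 1682
- Numerator 0.0922, denominator 193.1, so SE = 0.0219

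The detectable difference at 80% power is (1.960 + 0.842) × 0.0219 = 0.061, against 0.062 stated. Power for 0.1% is 99.6%, consistent with the stated figure of over 90%. If 1.5 is taken as the within-practice SD, the SE is 0.0224 and the detectable difference 0.063. The stated design reproduces. The article gives no figure for the attender subgroup.

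**3. Size of the selection term on the per-step reading (illustration)**

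From Background: 8.3% attended within 12 months of diagnosis, and education lowers HbA1c by about 0.4%. The following are assumptions, not document figures: attendance rises to 16.6% or 25%; the correlation ρ between propensity to attend and HbA1c lies between −0.2 and +0.2; and the package acts only through attendance.

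The mean HbA1c shift among attenders is SD × ρ × φ(z)/p, where p is the proportion attending. φ(z)/p is 1.842 at 8.3%, 1.501 at 16.6% and 1.271 at 25%. The contrast is intervention minus control, computed before rounding:

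| Attendance in intervention state | True all-patient effect | Attender contrast, ρ = −0.2 | ρ = 0 | ρ = +0.2 |
|---|---|---|---|---|
| 16.6% | −0.4 × 0.083 = −0.033 | +0.102 | 0 | −0.102 |
| 25% | −0.4 × 0.167 = −0.067 | +0.171 | 0 | −0.171 |

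The attender columns are the same whether the education effect is 0 or −0.4%, because that effect cancels. At ρ = 0 the contrast is null despite a real 0.4% benefit.

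**4. What an all-patient estimate could deliver**

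The complier-average effect is the all-patient effect divided by the difference in attendance. Its SE is roughly 0.02185 divided by that difference, treating the difference as known:
- 10-point rise: 0.22
- 15-point rise: 0.15
- 25-point rise: 0.09

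The rises are assumed. At 10 points the 95% half-width is 1.96 × 0.2185 = 0.43, and power for 0.4% is Φ(0.4/0.2185 − 1.96), about 45%.

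**The case against.** Several points on the other side stand.
- **Weight in the plan.** Item (1) is one of five secondary subgroup entries, and the article gives it no purpose of its own. A reader might infer that it is the designated explanation of a small overall effect. The text does not say so: the Discussion speaks of secondary analyses in general.
- **The ITT label.** A reader might infer that the article passes off attenders as the ITT population. 'ITT model' can fairly mean the form of the model, since the population is defined separately. The attender result should still not be presented as ITT.
- **Zero difference.** A reader might infer that the attender contrast must be null. That follows only on the per-step reading with no selection, and the article does not fix the reading. A precise attendance window is ordinary detail for the analysis plan.
- **Assumed figures.** The attendance rises and correlations above are illustrative. The article states no standard error.
- **The instrumental-variable remedy.** The package also works through staff roles, marketing, patient-facing resources and online education (Intervention section). Effects on HbA1c that bypass coded attendance are plausible.
- **Wording.** 'Offered' in item (5) is not attendance. 'Referred' in the Discussion is not tied to item (1), so it is a mismatch to tidy and not a proven contradiction.

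None of this restores randomisation to a contrast among attenders. It limits how strongly the point can be put and what can be required in its place.

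**Conclusion.** The point holds for item (1) and for 'attended' in item (5). Both select on behaviour that can follow randomisation and that the package targets. On either reading of 'attended', the contrast does not estimate the causal effect that the Discussion wants from the secondary analyses, unless attenders are exchangeable between the two states. The article states no such assumption.

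On the illustrative inputs, selection alone can match or exceed the 0.1% design difference, in either direction. The structural conclusion does not depend on those inputs.

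The primary analysis keeps all eligible patients and is untouched. Items (2) to (4) rest on baseline or patient characteristics and are outside this point. It would go too far to say that a complier-average estimate must replace item (1), because the exclusion restriction is open to doubt and precision may be poor.

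**What to change.** 1. State that item (1), and any grouping by programme attended in (5), is a non-randomised, descriptive analysis that will not support a causal claim. Do not present it as ITT.
2. Base (5) on the programme type available to the practice at month 0.
3. Make 'attended' in Analysis methods and 'referred' in the Discussion agree.
4. If an effect in attenders is wanted, add a complier-average (instrumental-variable) estimate in all eligible patients. Use randomised arm-by-step as the instrument for attendance by that step, adjusting for step and practice clustering. State the exclusion restriction and say how online education counts.
5. Extract attendance separately for each measurement period. Taking the last recorded code with months 9 and 18 extracted together may overwrite an earlier attendance.

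The cost is a few lines in the analysis plan, which the article says will be agreed before data release, one extra model, and a change to the extraction specification. It should not be assumed that the data needed are already in hand: the article describes only baseline data as collected, and collection runs to August 2021. The main drawback of step 4 is the low precision shown above if uptake rises little.
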